**Fig. 4 Fig4:**
[figure not shown]
The *Si shencong* acupoints (EX-HN1)

### Rehabilitation Treatment

Children with CP will undergo the routine rehabilitation programs as mentioned above. The rehabilitation programs will be carried out three times a week (once every other day) for 12 weeks and each session of the rehabilitation treatment (PT and OT) will last approximately 1 h. All rehabilitation treatments will be carried out by qualified therapists.

### Follow-up

After the 12-week treatment observation, all patients will start an additional 12-week follow-up period. CP patients from both groups will continue to attend rehabilitation treatment in the follow-up period. However, all patients from both groups are free to choose whether to receive scalp acupuncture or not with consent from his/her parents who have given their informed consent during the follow-up period. During the 12-week follow-up period, all of the CP patients from both groups will be reassessed by GMFM, FMFM, PEDI and CP-QOL at week 24 and will be asked to fill out forms to record their rehabilitation treatment attendance. All assessment scales and forms will be returned to the researchers for review at the end of the trial.

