### Safety

We will conduct the following tests on all participants at the screening stage to exclude patients with serious organic lesions: white blood cell count, platelet count, haemoglobin, coagulation function, creatinine, blood urea nitrogen, alanine aminotransferase/aspartate aminotransferase, gamma-glutamyl transpeptidase and electroencephalogram examination.

The subjects will be requested to report information about adverse events (AEs). All AEs that occur during the trial period will be recorded, such as dizziness, sweating, fainting, pallor, perturbed or chest congestion during scalp acupuncture treatment, local anaphylaxis, bleeding, unbearable prickling, local hematoma, retained needle after treatment and continuous severe local pain for more than 1 hour after acupuncture. The researcher will confirm the occurrence of AEs and record all details such as the time of occurrence, date, degree, measurement related to the acupuncture treatment and causal relationship with the acupuncture treatment. Serious AEs must be reported to the principal investigator immediately [10].

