### Data collection, management and monitoring

The CRF, Treatment Form and Adverse Events Form will be the first to be completed and then double-entered into the electronic data capture (EDC) system by two independent investigators, who will act as the first level of control to ensure the accuracy of the data. The second level of data integrity will include data monitoring and validation, which will be performed periodically throughout the study. The original CRFs and all other forms (including the consent forms) will be archived securely in the Clinical Trail Unit (CTU) of the Children’s Hospital affiliated with Fudan University for 5 years following publication of the last paper or report from the study [10].

The safety of the study will be monitored by a data and safety monitoring board (DSMB) of the CTU of the Children’s Hospital affiliated with Fudan University, which consists of independent clinical experts and statisticians with access to unblinded data. The DSMB is independent from the sponsor, the competing interests and the investigational site and will review the performance and safety of the trial monthly [10].

The criteria for unblinding and discontinuing allocated interventions for a given trial participant include acquiring a severe disease, having serious complications of CP or experiencing serious acupuncture-related AEs (if any), which have been described previously. The DSMB will reveal a participant’s allocated intervention and make the final decision to terminate the trial [10].

The final trial dataset will be under the custody of the Children’s Hospital affiliated with Fudan University. The data manager from the CTU of Children’s Hospital affiliated with Fudan University will have access to the complete, anonymous final dataset. Access to the final dataset or identifiable data by others will require written requests to be approved by the DSMB of the CTU of Children’s Hospital affiliated with Fudan University and all study investigators [10].

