### Statistical analysis

The Statistical Product and Service Solutions (SPSS) statistical package program (version 20.0, SPSS Inc., Chicago, Ill., USA) will be used to analyse data in the CTU of Children’s Hospital affiliated with Fudan University by statisticians. All analyses, including those from any participants who drop out during the trial, will be based on the intention-to-treat (ITT) principle using the last observation carried forward rule. Missing values will be handled by the mixed model for repeated measurements. Baseline information will be collected before randomization and includes the gender and age of patients, disease course, clinical type, GMFCS level, primary outcome (GMFM, FMFM) and secondary outcomes (PEDI, CP-QOL). Descriptive statistics will be used to detail baseline participant demographics and the general status of patients, such as gender, age, disease course, clinical type and GMFCS level. Variables will be checked for normal distribution and presented as mean +/− the standard deviation and compared by Student *t* test when normally distributed. For variables not normally distributed, the data will be expressed as median +/− the interquartile range, and non-parametric tests will be used. Categorical variables will be expressed as number (%) and analysed by *χ*^2^ tests or Fisher’s exact tests, when appropriate. The mixed effect model will be used to analyse the between-group difference in repeated measures for the two primary outcomes and other outcomes (GMFM, FMFM, PEDI and CP-QOL scores) across five testing time points (weeks 0, 4, 8, 12 and 24). Mean group difference and 95% confidence intervals will be reported. Safety analyses will be compared with the incidence of AEs in the two groups using the *χ*^2^ test. A *p* value of < 0.025 will be considered as statistically significant for the two primary outcomes.

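### The trial is sized on week 12, but the primary mixed model runs to week 24 with no visit named, although acupuncture is optional in both arms after week 12

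*Protocol article*

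**What the plan says.** All references are to the protocol article.

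- *Interventions*: scalp acupuncture is assigned for 12 weeks, three times a week.
- *Follow-up*: for the next 12 weeks, "all patients from both groups are free to choose whether to receive scalp acupuncture or not". Control children may therefore start it and treated children may stop. In the same period families "will be asked to fill out forms to record their rehabilitation treatment attendance"; acupuncture is not mentioned as an item.
- *Primary outcome measurement*: GMFM and FMFM are assessed at every visit, week 24 included, and no visit is singled out.
- *Statistical analysis*: "The mixed effect model will be used to analyse the between-group difference in repeated measures for the two primary outcomes", and for the other outcomes, "across five testing time points (weeks 0, 4, 8, 12 and 24". Then: "Mean group difference and 95% confidence intervals will be reported". The threshold for each primary outcome is 0.025. No visit is attached to the difference or to the test.
- *Sample size calculation*: the only place that commits to a time point. It assumes a 2.4-point difference in GMFM change after 12 weeks, SD 3.0, alpha 0.025, power 0.9 and 40 evaluable children per group.
- *Safety* and *Statistical analysis*: "All AEs that occur during the trial period will be recorded", and "Safety analyses will be compared with the incidence of AEs in the two groups", with no cut-off at week 12.

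**The concern.** The objective is whether scalp acupuncture improves motor function, and up to week 12 the randomised groups answer it. At week 24 they differ in what they were first assigned, while current acupuncture use in both groups is a matter of family choice. A week-24 difference by assigned group is a legitimate quantity, but it answers what happens when children start with or without acupuncture and then choose.

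As written, the primary result could be an average over visits, the week-12 contrast or the week-24 contrast, and the choice could be made after the data are seen. The trial's power statement covers only the second. A small week-24 difference would also be hard to interpret: it could reflect waning benefit, uptake by controls or stopping in the treated group, and the follow-up form as described would not separate these.

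The adverse event comparison shares the problem. Most of the listed events are needling events, and after week 12 such events can arise in either arm.

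**Working it through.** **1. The plan's own figure.** With difference 2.4, SD 3.0, two-sided alpha 0.025 (z = 2.2414) and power 0.9 (z = 1.2816):

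n per group = 2 × (2.2414 + 1.2816)² × (3.0/2.4)² = 2 × 12.41 × 1.5625 = 38.8, so 39.

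The t-based calculation gives 41, with power 0.899 at 40 per group (0.909 by the normal formula). The stated 40 is reproduced, and 40/0.80 = 50 per group. The sidedness of alpha is not stated; one-sided 0.025 would need only 33 or 34, so two-sided is the reading that fits. The figure rests on the week-12 contrast. No FMFM difference or SD is given, so the power figures here concern GMFM only.

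**2. If the test averages over visits, rising effect.** Assumptions, none of them in the document: true differences 0.8, 1.6 and 2.4 at weeks 4, 8 and 12; score SD 15 with a random child intercept; visit error variance 4.5, so that change has variance 2 × 4.5 = 9, the planned SD of 3.0. The between-child variance is 225 − 4.5 = 220.5. Given baseline it is 220.5 × 4.5/225 = 4.41. A baseline-adjusted mean of k visits has variance 4.41 + 4.5/k per child, and the group difference has SE = √(2 × variance/40). If a share c of controls take up acupuncture and gain the full effect, while treated children keep theirs, the week-24 difference is 2.4 × (1 − c). Power = Φ(estimate/SE − 2.2414).

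| Quantity tested | Week-24 difference | Estimate | SE | Power |
|---|---|---|---|---|
| Week 12 only | not used | 2.40 | 0.667 | 91% |
| Average, weeks 4–12 | not used | 1.60 | 0.544 | 76% |
| Average, weeks 4–24, c = 0 | 2.40 | 1.80 | 0.526 | 88% |
| Average, weeks 4–24, c = 20% | 1.92 | 1.68 | 0.526 | 83% |
| Average, weeks 4–24, c = 30% | 1.68 | 1.62 | 0.526 | 80% |
| Average, weeks 4–24, c = 50% | 1.20 | 1.50 | 0.526 | 73% |
| Average, weeks 4–24, contrast gone | 0 | 1.20 | 0.526 | 52% |

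At 20% or 30% uptake, adding week 24 gives more power than averaging weeks 4–12 alone; at 50% it costs 3 points. Unless most of the week-24 contrast disappears, the larger loss comes from averaging in the early visits.

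**3. If the effect is flat.** Take 2.4 at weeks 4, 8 and 12, and let q be the share of the week-24 contrast lost. The four-visit average is (3 × 2.4 + 2.4 × (1 − q))/4: 2.4 at q = 0, 2.1 at q = 0.5 and 1.8 at q = 1. With change SD 3.0 at each visit and correlation ρ between visits, the SD of the average is 3.0 × √((1 + 3ρ)/4). For ρ = 0.5, 0.7 and 0.9, power is:

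- q = 0: 0.99, 0.97, 0.93
- q = 0.5: 0.957, 0.906, 0.845
- q = 1: 0.88, 0.79, 0.71
- weeks 4–12 average, for comparison: 0.98, 0.96, 0.93

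Here week 24 does dilute, although power can stay above 0.9 when ρ is low and the loss is partial.

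**4. If the test is read at week 24 alone.** With 40 per group and SD 3.0, t-based power is 72% at c = 20% (difference 1.92), 59% at 30% (1.68) and 32% at 50% (1.20).

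**5. If the week-12 contrast is named.** With group-by-visit terms and complete data, week-24 behaviour does not enter it. The difference stays 2.4 and power about 0.90 at 40 per group.

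**The case against.** The strongest reply is that the article never says the visits are averaged. The model terms are not given, the list of time points includes week 0, where no effect can exist, and the sample size and the follow-up label both suggest week 12 as the intended focus. A group-by-visit model with a week-12 contrast would fit the text and avoid nearly all of the problem. This stands in part: pooling is a possible reading and not a stated fact. But the text does not commit to that contrast, and choosing the confirmatory visit is more than a detail of model coding when the last visit follows a change in treatment conditions.

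A reader might infer more from these passages. Four inferences are not supported:

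- *That the whole between-group comparison is contaminated.* Optional acupuncture begins after week 12, so weeks 4 to 12 are unaffected.
- *That including week 24 necessarily costs power, or that the trial's power is 72%, 59% or 32%.* Those figures belong to a week-24-only test, which nothing makes primary, and under a rising effect moderate uptake still leaves week 24 adding power.
- *That follow-up acupuncture goes unrecorded.* The section on data collection says "The CRF, Treatment Form and Adverse Events Form will be the first to be completed". That Treatment Form's content and period are not described, so it may cover the sessions. All that can be said is that no such record is described for weeks 12 to 24.
- *That the adverse event difference is biased towards zero.* Treated children who continue acupuncture also add events, so the direction depends on uptake in both arms. Event dates and relation to acupuncture are recorded, so a split at week 12 is feasible.

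**Conclusion.** The point holds as a mismatch between design and analysis. The sample size rests on a week-12 difference, while the primary analysis extends to a visit at which acupuncture is optional in both arms and leaves open which visit decides the trial. The week-24 difference estimates initial assignment followed by free choice; only that visit is affected.

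The size cannot be fixed from the document. Under the rising-effect assumptions, a four-visit average gives an estimate of 1.2 to 1.8 and power of 52% to 88%. Under a flat effect it gives 1.8 to 2.4 and power of 0.71 to 0.99. These ranges rest on assumed uptake, effect path, score SD and between-visit correlation. What does not depend on the uptake assumption is that the week-12 contrast keeps the planned 2.4 and about 90% power for GMFM.

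**What to change.** 1. State that the confirmatory test of each primary outcome, at 0.025, is the week-12 between-group contrast from a mixed model with group-by-visit terms.
2. Report week 24 as a separate secondary comparison by initial assignment, outside the 0.025 tests, and describe it as assignment followed by optional acupuncture.
3. Add the number and dates of acupuncture sessions in weeks 12 to 24 to the existing follow-up form, or state that the Treatment Form captures them, and tabulate by arm.
4. Make the main adverse event comparison by arm for weeks 0 to 12. List events in weeks 12 to 24 separately by acupuncture actually received, using the dates already collected.

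The cost is wording and one form item; care, visits and sample size do not change. Week 24 no longer supports a confirmatory claim. The form item is the urgent part, since sessions not logged at the time may not be recoverable later.

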## Abstract

**Background:**

Scalp acupuncture has been widely used as treatment for motor dysfunction in children with cerebral palsy in China. Previous studies have failed to provide high-quality evidence to demonstrate the effectiveness of this treatment in children with cerebral palsy. No high-quality randomized controlled trials on scalp acupuncture have been published. The aim of this study is to evaluate the effectiveness of Jiao’s scalp acupuncture when combined with routine rehabilitation treatment versus routine rehabilitation treatment alone for motor dysfunction in children with cerebral palsy.

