### Primary outcome measurement

The two primary outcomes of the study—Gross Motor Function Measure (GMFM) and Fine Motor Function Measure Scale (FMFM)—will be assessed at baseline, during the intervention period (at 4 weeks, 8 weeks and 12 weeks) and in the follow-up period (at 24 weeks).

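### Week 24, when children in both arms may be taking scalp acupuncture by choice, sits in the mixed model for both primary outcomes and no primary time point is named

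*Protocol article*

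**What the plan says.** The Abstract (Background) sets the question as "Jiao’s scalp acupuncture when combined with routine rehabilitation treatment versus routine rehabilitation treatment alone".

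The Follow-up section states that after the 12-week treatment period "all patients will start an additional 12-week follow-up period". Rehabilitation continues in both groups during that time, and "all patients from both groups are free to choose whether to receive scalp acupuncture or not", with parental consent. Families "will be asked to fill out forms to record their rehabilitation treatment attendance". No form for scalp acupuncture in weeks 12 to 24 is named there.

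Primary outcome measurement lists GMFM and FMFM at baseline, at weeks 4, 8 and 12, and "in the follow-up period (at 24 weeks".

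Statistical analysis states: "The mixed effect model will be used to analyse the between-group difference in repeated measures for the two primary outcomes", and for the other outcomes, "across five testing time points (weeks 0, 4, 8, 12 and 24". Mean group differences with 95% confidence intervals are to be reported, and p < 0.025 is the threshold for the two primary outcomes. All analyses "will be based on the intention-to-treat (ITT) principle using the last observation carried forward rule". No visit is singled out as primary.

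Sample size calculation assumes a between-group difference of 2.4 points in GMFM change after 12 weeks of treatment (SD 3.0). With alpha 0.025 and power 0.9 it gives 40 per group, raised to 50 per group for 20% dropout.

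**The concern.** The contrast created by randomisation, rehabilitation with or without scalp acupuncture, is maintained only to week 12. After that a control child may start the tested treatment, and a child in the acupuncture arm may continue or stop. The week-24 difference between arms therefore mixes three things: what remains of the 12-week course, delayed treatment in controls, and further treatment in the acupuncture arm. It is not the add-on comparison in the stated aim, nor a measure of durability after stopping.

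This would matter little if week 24 were plainly a secondary visit. As written, it stands in the same model as the earlier visits, for both primary outcomes, and nothing says which contrast from that model decides the trial. A difference taken over all visits, or the week-24 difference itself, could carry the primary claim. Control uptake would pull such an estimate down, and continued use in the acupuncture arm could push it up. If uptake is not captured, readers cannot tell which happened.

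**Working it through.** **Inputs from the protocol (Sample size calculation):** difference 2.4, SD 3.0, alpha 0.025, power 0.9, 40 per group, 20% dropout. **Assumed, because the protocol gives no figure:** uptake rates in weeks 12 to 24, the gain in children who take up acupuncture, and equal weighting of visits in an overall difference.

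**1. The plan's own figure.** With two-sided alpha 0.025, n per group = 2 × (2.241 + 1.282)² × 3.0² / 2.4² = 38.8, so 39 by the normal approximation and 41 by the noncentral t. The stated 40 lies between them. Dropout: 40 / 0.8 = 50 per group, 100 in total. One-sided 0.025 gives 33 or 34 and does not match. At 40 per group the power is 0.909 (normal) or 0.899 (noncentral t). The design is tied to the week-12 effect.

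**2. Week-24 difference under control uptake.** Suppose the 2.4 points are kept in the acupuncture arm and a fraction c of controls start and gain the full 2.4 by week 24. The week-24 difference is then 2.4 × (1 − c).

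**3. Overall difference.** With 2.4 at weeks 4, 8 and 12 and equal weights, the average is (3 × 2.4 + week-24 difference) / 4. Power is by the noncentral t with 40 per arm, SD 3.0 and two-sided 0.025.

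| Control uptake c | Week-24 difference | Average over weeks 4–24 | Power for the average |
|---|---|---|---|
| 0% | 2.40 | 2.40 | 0.899 |
| 30% | 1.68 | 2.22 | 0.845 |
| 50% | 1.20 | 2.10 | 0.799 |
| 70% | 0.72 | 1.98 | 0.746 |

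The SD of 3.0 is the planning value for change at week 12. The SD of an average over visits would generally differ, so the drop in power indicates size and is not a forecast.

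**4. Week 24 taken alone.** If that visit carried the claim, power for the same differences would be 0.588, 0.315 and 0.118.

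**5. The other direction.** If 80% of the acupuncture arm continue, 20% of controls start and gains are fully additive, the week-24 difference is 2.4 + 0.8 × 2.4 − 0.2 × 2.4 = 3.84, which is 60% above the 12-week effect. The equal-weight average is then (3 × 2.4 + 3.84) / 4 = 2.76.

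**6. Week-12 contrast.** Optional acupuncture begins after this visit, so the week-12 difference stays at 2.4 and power at 0.899 in every scenario.

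**The case against.** A mixed model with visit-specific arm effects can include week 24 and still yield a clean week-12 contrast. The Statistical analysis section does not say that one time-averaged difference is the primary test, and the sample size points to week 12. Analysed as randomised, the week-24 difference is also a valid treatment-policy comparison of initial assignment followed by free choice. The article states no durability objective and calls week 24 follow-up. It is also a condensed report, so form content and the extracted contrast may be set out elsewhere.

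Much of this stands, and it limits the point in three ways:

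- A reader might infer that acupuncture uptake goes unrecorded. The article supports only that no such record is named. It lists a Treatment Form under Data collection, management and monitoring without saying whether it covers weeks 12 to 24.
- A reader might infer that the plan pools all visits into one primary difference. That is one possible reading, not the text.
- A reader might take the power of 0.588, 0.315 or 0.118 as the power of the primary analysis. Those values belong to a stand-alone week-24 test, which the protocol neither sizes nor names as primary. Dilution of an average over visits is much milder.

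The objection does not remove the stated combination: free choice in both arms after week 12, week 24 among the primary-outcome visits in the model, and no primary visit named. The treatment-policy question is legitimate, but the article does not state it as its aim, and it differs from the add-on question in the Abstract.

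**Conclusion.** The concern holds in a limited form and should be fixed. As written, the plan allows a visit at which the randomised contrast is no longer maintained to contribute to, or carry, the primary claim for GMFM and FMFM.

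The size depends on uptake, which the protocol does not give. For an equally weighted average, 30 to 70% control uptake costs 0.18 to 0.42 points of the planned 2.4 (2.40 − 2.22 and 2.40 − 1.98) and about 5 to 15 percentage points of power. This assumes the full effect already at week 4, full gain in control starters and SD 3.0. Continued use in the acupuncture arm could reverse the direction. The week-12 contrast and the sample size are not affected, so the trial's central comparison is sound once it is named.

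**What to change.** 1. Make the week-12 between-group contrast the primary test for GMFM and for FMFM, each at 0.025, from a mixed model using visits up to week 12.
2. Add the number and dates of scalp acupuncture sessions in weeks 12 to 24 to the existing follow-up form, for both arms, unless another form already captures them.
3. Report week 24 as a secondary comparison as randomised, described as initial assignment followed by optional acupuncture in both arms. Show uptake by arm beside it and draw no conclusion about persistence from the plain difference.
4. A sensitivity analysis that sets aside week-24 values after uptake is optional. If it is done, it must not carry week-12 values forward, which the last-observation rule in Statistical analysis would otherwise do. It must also state its missing-data assumption, since families may choose acupuncture in the light of how the child has responded.

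The cost is a change of analysis wording, one item on a form already in use and one table. Sample size, visits and follow-up care stay as they are. The downside is that week 24 no longer supports the primary claim. Uptake is easy to record as it happens and hard to recover later, so the form item should come first.
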